#### 5.2.9. Mood

The Profile of Mood States-Adolescents [64], validated in adults [65], assesses current mood across 6 sub-components including anger, confusion, depression, fatigue, tension, and vigour. Twenty-four items are rated based on the extent to which participants are experiencing them “right now”, rated 0 (not at all) to 4 (extremely).

#### 5.2.10. Pulse Rate and Blood Pressure

Pulse rate and blood pressure will be measured using an Omron HEM-7600T electronic upper-arm blood pressure monitor. These are designed for use by untrained lay-persons [66] but will be conducted by PCCS staff.

## 6. Outcomes of interest

### 6.1. Primary Outcomes

Global Quality of Life—WHOQoL-Bref [56]Social Adjustment—Work and Social Adjustment Scale [59]Loneliness UCLA 3-item Loneliness Scale [60]

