#### 5.2.2. Quality of Life

The World Health Organisation Brief assessment of QoL [56] assesses QoL over the previous 2 weeks. It is validated in adults with mental illness [57] and has good discriminant, content, and test-retest reliability [58]. Two overall items assess overall QoL and physical health, and four domains including social relationships, physical health, psychological health, and environment. Items are rated on a Likert scale from 1 (not at all/very poor) to 5 (completely/very good).

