## 7. Statistical Analysis

### 7.1. Sample Size Estimation

A priori power calculation is based on self-reported quality of life WHOQoL-Bref [56] with reference values for mean and standard deviation taken from Spinal Cord Injury Research Evidence [67] and methods from Rosner [68]. Assumptions include α = 0.05, β = 0.2, and power = 0.8 (80%). Calculations indicate a sample of 126 participants is required to detect a minimum effect of 0.5 units (SD = 19.4) between control and intervention conditions post-intervention. We aimed to recruit 140 participants to allow for an attrition rate of 11%, i.e., between the 7% median attrition rate of RCTs [69] and estimated 12.9% in mental illness research [70].

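### Section 7.1 misstates its detectable difference: 126 participants follow from 0.5 SD (9.7 points at SD 19.4), not 0.5 units, and the WHOQoL-Bref score with that SD is not named

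*Protocol article*

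**What the plan says.** Section 6.1 (Primary Outcomes) names "Global Quality of Life—WHOQoL-Bref" as one of three primary outcomes, without saying which score this is.

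Section 5.2.2 (Quality of Life) describes the instrument: "Two overall items assess overall QoL and physical health, and four domains including social relationships, physical health, psychological health, and environment". The only scale it gives is the item response format: "Items are rated on a Likert scale from 1 (not at all/very poor) to 5 (completely/very good"). It describes no total score and no rescaled score.

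Section 7.1 (Sample Size Estimation) says: "A priori power calculation is based on self-reported quality of life WHOQoL-Bref", with "reference values for mean and standard deviation taken from Spinal Cord Injury Research Evidence". It adds: "Assumptions include α = 0.05, β = 0.2, and power = 0.8 (80"%). From these it concludes that 126 participants are required "to detect a minimum effect of 0.5 units (SD = 19.4") between the control and intervention conditions. It does not say which WHOQoL-Bref score has this SD, or on what range.

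**The concern.** Two things in Section 7.1 look wrong when read beside Section 5.2.2.

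First, a difference of 0.5 on a score with SD 19.4 is a standardised effect of about 0.026. No conventional calculation would find that 126 participants can detect it. Either the unit of the 0.5 or the SD is misstated.

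Second, 19.4 is far too large for a score built from one or two items rated 1 to 5, and those overall items are the part of the instrument nearest to the label in Section 6.1.

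At stake is what the trial is designed to detect. From the text, a reader cannot tell whether the target is half a point on a five-point item or nearly ten points on some other scale. These are different claims about benefit, and the eventual result will be judged against one of them.

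**Working it through.** **Inputs.** From Section 7.1: difference 0.5, SD 19.4, α = 0.05, power 0.80, required N = 126. From Section 5.2.2: items scored 1 to 5, two overall items. Assumptions: a two-sided test (the article does not state the side), the normal approximation, and a simple comparison of two independent groups unless stated otherwise.

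**1. The plan's figure with its inputs as written.**
n per condition = 2 × (1.960 + 0.842)² × SD² / difference²
= 2 × 7.849 × 19.4² / 0.5² = 23,633 per condition, or 47,266 in total.

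Other readings of the same inputs do not rescue 126:

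| Reading | n |
|---|---|
| Two groups, one-sided | 18,615 per condition |
| Paired, SD of differences 19.4, two-sided | 11,817 |
| Paired, SD of differences 19.4, one-sided | 9,308 |
| Paired, SD 19.4 at each time, correlation 0.9 | 2,364 |
| Paired, correlation 0.99 | 237 |
| Paired, correlation 0.995 | 119 |

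A paired analysis comes near 126 only with a within-person correlation of about 0.995, which is not credible for a self-report questionnaire over 10 weeks.

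**2. Power if the inputs were literally true.** With 63 per condition, the standard error is 19.4 × √(2/63) = 3.46, and 0.5 / 3.46 = 0.145. Power = Φ(0.145 − 1.960) ≈ 3.5%, counting only rejections in the favourable direction.

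**3. Reading 0.5 as SD units.**
2 × 7.849 / 0.5² = 62.8, so 63 per condition and 2 × 63 = 126. This matches exactly.
At SD 19.4, the difference is 0.5 × 19.4 = 9.7 points. As a check, the detectable difference with 63 per condition is 2.802 × 19.4 × √(2/63) = 9.68.

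Put the other way, a raw difference of 0.5 gives 63 per condition only if the SD is about 1.0. So either the 0.5 is not in the units of the score with SD 19.4, or 19.4 is not the SD that was used.

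**4. Can the SD be 19.4 on the scale described?** The largest possible SD of a score bounded between a and b is (b − a)/2.
- One item, 1 to 5: (5 − 1)/2 = 2.0.
- Sum of the two overall items, 2 to 10: (10 − 2)/2 = 4.0.
- A score rescaled to 0-100 (an assumption; the article mentions none): 100/2 = 50.

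So 19.4 is impossible for the raw overall items and possible for a 0-100 score. If 19.4 is an SD on 0-100, a single item rescaled in this way would have SD 19.4 × 4/100 = 0.78 on its 1-5 scale. A rescaled overall item is therefore not excluded.

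**The case against.** The strongest reply has three parts.

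First, Section 5.2.2 gives a response format for items, not the range of the analysed score. The article describes most of its other questionnaires in the same way. Scoring and rescaling of a standard instrument are commonly left to a full protocol, an analysis plan or the cited manual. This stands: an unnamed score would not be a finding by itself.

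Second, a reader might infer that the primary outcome and the powered score are different variables, so that the stated power does not apply to the primary outcome. The documents do not support that. Sections 6.1 and 7.1 both speak only of WHOQoL-Bref quality of life. The mismatch appears only if the word global is taken to mean the raw overall items, which the article does not say. A rescaled item, domain or total could have SD 19.4, and the two could be the same score. Nor does anything in the article plan to test several scores under the global label, so a claim of inflated false positives has no footing.

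Third, a standardised effect has no scale, so 126 is the same for an item, a domain or a total. This also stands, and it limits the consequence.

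None of this repairs the printed pair of figures. A scoring rule held in another document cannot make 0.5 units with SD 19.4 yield 126.

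**Conclusion.** The stated detectable difference is wrong as printed. Taken literally, it needs about 23,600 per condition, against the 63 per condition that 126 implies. The figure of 126 is reproduced by a difference of 0.5 SD, which is 9.7 points at SD 19.4 and about 19 times the printed 0.5 (9.7 / 0.5 = 19.4). This rests on two independent groups, a two-sided 5% test and 80% power.

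The SD of 19.4 implies a WHOQoL-Bref score that the article does not identify. Whether it is the score meant in Section 6.1 cannot be determined from the article.

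A reader might also conclude that the trial has 3.5% power. That goes too far: the exact match at 0.5 SD points to a misreported unit (or SD), not to a sample size derived from the literal inputs. Under that reading N stays at 126. What changes is the size of effect the trial can claim to detect.

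**What to change.** In Section 7.1, restate the detectable difference as 0.5 SD, adding 9.7 points if SD = 19.4 is retained. In Sections 6.1 and 7.1, name the single WHOQoL-Bref score, with its range, to which that SD and difference apply. If the primary score is a raw 1-5 item, replace both the SD and the difference with values on that scale.

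The cost is wording in two sections, plus a check of the source of the SD to confirm which score it describes. No extra participants or data are needed, and under the 0.5 SD reading the required 126 stands.

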### 6.2. Secondary Outcomes

#### 6.2.1. Mental Health

Depression—Patient Health Questionnaire-9 [61]Anxiety—Generalised Anxiety Disorder Questionnaire [62]

#### 6.2.2. Health Self-efficacy

The Health Confidence Score [63]

#### 6.2.3. Physical Health

Physical Health Subscale of WHO-QoL-Bref [56]

#### 6.2.4. Health Service Utilisation

Frequency of ambulance use, hospital visits, hospital admissions, nights spent in hospital, GP visits, allied health, and community health service utilisation.

## 7. Statistical Analysis

### 7.1. Sample Size Estimation

A priori power calculation is based on self-reported quality of life WHOQoL-Bref [56] with reference values for mean and standard deviation taken from Spinal Cord Injury Research Evidence [67] and methods from Rosner [68]. Assumptions include α = 0.05, β = 0.2, and power = 0.8 (80%). Calculations indicate a sample of 126 participants is required to detect a minimum effect of 0.5 units (SD = 19.4) between control and intervention conditions post-intervention. We aimed to recruit 140 participants to allow for an attrition rate of 11%, i.e., between the 7% median attrition rate of RCTs [69] and estimated 12.9% in mental illness research [70].

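### The stated 126 participants, 0.5-unit effect, SD of 19.4 and 80% power cannot all hold; 126 fits an effect of 0.5 standard deviations, so the effect appears to be mislabelled

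*Protocol article*

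**What the plan says.** Section 7.1 bases the sample size on one outcome: "A priori power calculation is based on self-reported quality of life WHOQoL-Bref". The error rates are given as "Assumptions include α = 0.05, β = 0.2, and power = 0.8 (80"%); sidedness is not stated. The result is that "a sample of 126 participants is required to detect a minimum effect of 0.5 units (SD = 19.4"), comparing the two conditions after the intervention. The mean and SD are attributed to an external reference source and the method to a textbook. The recruitment target follows: "We aimed to recruit 140 participants to allow for an attrition rate of 11"%, a rate chosen between two cited figures, 7% and 12.9%.

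Three other places bear on this. Section 2.1 has every participant complete a control period and then the intervention, so that each serves as their own control within a stepped-wedge cluster design. Section 5.2.2 describes the WHOQoL-Bref as two overall items and four domains, with items scored 1 to 5. Section 6.1 lists global quality of life as one of three primary outcomes. Section 7.1 does not say which WHOQoL-Bref score, or which scale, the 0.5 and the 19.4 refer to.

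**The concern.** An effect given in units next to a raw SD reads as scale points. On that reading the trial would detect a change of about one fortieth of a standard deviation with 126 people, which is not possible under any usual design assumption.

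The planned detectable effect is the basis for calling the sample adequate. The Introduction and the Discussion both present sample size as an advance over earlier social prescribing studies. If the effect is mislabelled, the stated sensitivity is 19.4 times finer than the one the formula was apparently run for (0.5 against 9.7 units), and a results paper that repeats the sentence would carry the error forward.

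This is not a detail left to an analysis plan. The effect, SD, alpha, power and sample size are all stated, and they disagree.

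**Working it through.** **Inputs (Section 7.1):** alpha 0.05, power 0.80, effect 0.5 units, SD 19.4, N = 126, 11% attrition, 140 recruited. **Assumptions:** two-sided test unless noted; within-person correlation (rho), which the article does not give, varied from 0 to 0.9 and beyond. Clustering is ignored throughout.

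**1. Reproducing 126.** For two equal groups, n per group = 2(1.96 + 0.8416)² / d².
- With d = 0.5: 2 × 7.849 / 0.25 = 62.8, so 63 per group and **126 in total**. At SD 19.4, d = 0.5 is 0.5 × 19.4 = 9.7 units.
- This match is by the normal approximation. By the t-test, 63 per group gives 79.5% power and 64 per group (128 in total) gives 80.1%.

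**2. The effect as written.** d = 0.5 / 19.4 = 0.0258.

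| Reading | N needed for 80% power |
|---|---|
| Two groups, two-sided | 23,633 per group, 47,266 in total |
| Two groups, one-sided | 18,615 per group, 37,230 in total |
| Paired, SD of the difference 19.4 | 11,817 |
| Paired, rho 0.9 | 2,364 |
| Paired, rho 0.99 | 237 |
| 19.4 read as a variance | 1,219 per group, or 610 pairs |

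For 126 pairs to suffice, the SD of the difference would have to be 0.5 × √126 / 2.8016 = 2.0, which means rho of about 0.995.

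**3. Power of 126 people for 0.5 units** (t-based).
- 63 versus 63: 5.2%.
- Paired, with SD of the difference = 19.4 × √(2(1 − rho)):

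| rho | 0 | 0.3 | 0.5 | 0.7 | 0.9 | 0.95 | 0.99 |
|---|---|---|---|---|---|---|---|
| Power, two-sided | 5.5% | 5.7% | 5.9% | 6.6% | 9.8% | 14.8% | 52.8% |

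- Paired and one-sided: 7.5% at rho 0, rising to 15.8% at rho 0.9.

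**4. Other routes to 126.**
- A paired or one-sample calculation at d = 0.25 gives 7.849 / 0.0625 = 125.6, also 126. If 19.4 is the SD of within-person change, that effect is 0.25 × 19.4 = 4.85 units.
- Half a raw unit with an SD of about 1.0 also gives 63 per group, but 1.0 is not the stated SD. Conversely, an SD of 19.4 cannot belong to a single item scored 1 to 5, whose SD is at most about (5 − 1) / 2 = 2. The scale therefore has to be named.

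**5. Attrition.** 140 × 0.89 = 124.6, below 126. The exact inflation is 126 / 0.89 = 141.6, so 142, whereas 126 × 1.11 = 139.9 gives the stated 140. The loss that 140 covers is 1 − 126/140 = 10.0%. At 62 versus 62 and d = 0.5, t-test power is 78.9%, against 79.5% at 63 versus 63.

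**The case against.** The strongest reply is that this is a labelling slip and not a design failure. If the authors planned for 0.5 standard deviations, the trial was never sized for half a point, and neither recruitment nor analysis changes. That stands, and it is why the remedy is wording. It does not rescue the sentence, which gives a wrong detectable effect.

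Two further objections also stand. First, a reader might infer that 126 can arise only from 0.5 standard deviations. It cannot be put that strongly: a paired calculation at 0.25 gives 126 too, and the sources for the SD and the method are not at hand. The printed 0.5 makes the two-group reading the likeliest, but it remains an inference.

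Second, a reader might infer that 9.7 units is what this trial can detect. The article does not support that. Section 2.1 describes no comparison of 63 people with 63 others. With 126 people as their own controls, the difference detectable at 80% power would be about 5.7, 4.8 or 3.8 units at assumed correlations of 0.3, 0.5 or 0.7, before any allowance for clustering or period effects. The 9.7 describes the formula apparently used, not the trial.

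Nor does the error settle how a null result should be read. That rests on the estimate and its confidence interval; the error misstates planned sensitivity only.

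On attrition, the shortfall is two recruits. The 12.9% figure exposes no error, because the plan openly chose a lower rate.

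**Conclusion.** The inconsistency is real. With alpha 0.05, 80% power and SD 19.4, 126 people cannot detect 0.5 units. Two groups would need about 47,000. Two-sided power at 126 is about 5% as two groups, or about 5.5% to 10% as own controls, assuming a within-person correlation of 0 to 0.9. It exceeds 10% at higher correlations or with one-sided paired testing, and would reach 80% only at a correlation near 0.995, which is not stated and not plausible for a self-report scale measured weeks apart.

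The most likely explanation is a standardised effect of 0.5 reported as raw units, because that reproduces 126 under a two-sided, two-group normal approximation. It would be going too far to say that the trial has 5% to 10% power for the effect its authors intended, since they appear to have intended a much larger one.

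The attrition statement is wrong but minor: the allowance is 10.0%, and the consequence is less than one percentage point of power.

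**What to change.** Check the original calculation and replace the stated effect and SD in Section 7.1 with the effect actually used. If the two-group reading is confirmed, this would be: 0.5 standard deviations (9.7 units at SD = 19.4), two-sided. Name the WHOQoL-Bref score and the scale on which the SD is expressed. Add a sentence saying that the figure is for an independent two-group comparison of individuals, that it ignores clustering and the own-control stepped-wedge design, and that it is therefore not the trial's actual detectable effect.

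Restate the attrition allowance as 10%, or say that 11% loss would leave about 124 participants.

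The cost is wording only. The stated sensitivity becomes less favourable, and no extra participants are needed.

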## 4. Intervention

The intervention will include 10 weekly 90-min FT sessions in groups of 6–10. Sites include Gold Coast Baree-Badalla Reserve—public nature reserve, mangrove biome, 1.2 km pathed footpath [52]; and Sydney Ku-ring-gai Wildflower Garden—‘senses tracks’, 900 m, forest biome, flat unpaved track [53]. Sessions will be facilitated by a certified FT Guide [54] and accompanying PCCS health workers (mental health nurse/allied health) with a maximum ratio of 1 staff member to 3 participants. Intervention objectives and prescribed activates follow the guidebook of the International Nature and Forest Therapy Alliance [54].

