#### Analysis

Data will be entered, cleaned, checked, and analysed in SPSS 27 [71]. Within and between-group analysis will be conducted with differences considered significant at α = 0.05. Analysis will be conducted according to the methods of Hussey and Hughes [72] who have produced a guide to analysis for the (relatively new) stepped-wedge cluster design. A Linear Mixed Model (LMM) will be used as this allows for non-independence in the data including clustering and repeated measures. Weighted Least Squares (Weighted Linear Regression) will be used to estimate the fixed effects. Subgroup analysis will examine differences across mental illness diagnoses. Assessment tools missing <20% responses will be imputed with participant tool mean. Tools with >20 missing responses will be excluded.

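### The 80% power at N = 126 fits two independent groups with no clustering or repeated measures, so it is not the power of this stepped-wedge cohort; the direction of the error is unknown

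*Protocol article*

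**What the plan says.** Section 7.1 bases the sample size on the WHOQoL-Bref, with α = 0.05 and 80% power. "Calculations indicate a sample of 126 participants is required" to detect a smallest effect of 0.5 units, with SD 19.4, "between control and intervention conditions post-intervention". The inputs are "reference values for mean and standard deviation taken from Spinal Cord Injury Research Evidence", and the method is credited to a general biostatistics text. The recruitment target of 140 is then built on 126 with an attrition allowance. The section gives no intra-cluster correlation, within-person correlation, cluster count, number of steps or period effect.

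The design is described elsewhere in the article. Section 2.1 sets out a stepped-wedge cluster trial. Every participant passes through a 10-week control period and then the intervention, with five main assessments, and only the order in which clusters start is randomised. Section 4 gives the cluster size: "The intervention will include 10 weekly 90-min FT sessions in groups of 6–10". The Analysis subsection of section 7 says: "A Linear Mixed Model (LMM) will be used as this allows for non-independence in the data including clustering and repeated measures". Section 9.2 expects participants to resemble each other within sites and within clusters.

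**The concern.** The sample size section and the analysis section assume different data. The analysis treats observations as correlated within therapy group and within person. The power calculation appears to treat them as 126 unrelated people, half in each condition, measured once.

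The two omissions pull in opposite directions. Correlation within groups, and adjustment for calendar time in a staggered start, reduce information. Comparing people with themselves adds it. The published 80%, and the effect said to be detectable, could therefore be wrong either way.

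This matters because the Introduction presents the sample size as a remedy for weaknesses in earlier social prescribing studies, and the Discussion returns to sample size as a strength. A null result would be read against a power figure that belongs to another design.

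**Working it through.** **Inputs from section 7.1:** α = 0.05 (sidedness not stated; two-sided assumed because it reproduces N), power 0.80, effect 0.5, SD 19.4, N = 126. **From section 4:** groups of 6–10, so 126/10 to 126/6, or about 13 to 21 clusters. **Assumed, because the article gives no values:** ICC 0.01–0.10, within-person correlation, cluster autocorrelation, and 2 to 7 steps. The figure of study phases was not available.

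**1. Reproducing 126.** Unpaired two-sample normal formula with an effect of 0.5 SD (0.5 × 19.4 = 9.7 points):

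n per group = 2 × (1.960 + 0.842)² / 0.5² = 2 × 7.849 / 0.25 = 62.8, so 63 per group and 126 in total (power 80.1%).

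Alternatives:
- One-sided test: 100.
- Paired test at 0.5 SD of the difference: 7.849 / 0.25 = 31.4, so 32.
- Paired test at 0.25 SD of the difference: 7.849 / 0.0625 = 125.6, so 126. The article does not state that effect.
- Literal 0.5 points with SD 19.4: 2 × 7.849 × (19.4/0.5)² ≈ 23,633 per group, or 47,266 in total. With 126, power would be about 3%.

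Only the 0.5 SD unpaired reading uses the stated 0.5 and returns the stated N.

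**2. Clustering alone.** Design effect DE = 1 + (m − 1) × ICC; power = Φ(0.5 × √(126 / (4 × DE)) − 1.96).
- m = 6, ICC 0.01: DE 1.05, Φ(2.739 − 1.96) = 78%.
- m = 8, ICC 0.05: DE 1.35, 68%.
- m = 10, ICC 0.10: DE 1.90, Φ(2.036 − 1.96) = 53%.

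The N needed for 80% power would run from 133 to 240.

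**3. Own-control comparison alone**, with no clustering or time effect: N = 2(1 − r) × 7.849 / 0.25, which is 63, 32 and 13 at within-person correlation r = 0, 0.5 and 0.8. Power with 126 is 97.8% or more.

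**4. Both together, with period effects.** Generalised least squares on cluster-period means with fixed period effects, for about 126 participants in 14 to 21 clusters. In units of SD², each mean has variance [1 + (m − 1)ρ]/m. Two periods of the same cluster have covariance [r + (m − 1)ρc]/m, where ρ is the ICC, c the cluster autocorrelation and r the within-person correlation. Power = Φ(0.5/SE − 1.96).

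| Layout | 2 steps | 3 steps | 4 or more steps |
|---|---|---|---|
| A. Each cluster measured in one control and one FT period of its own | 55–78% | not tabulated | 95% or more |
| B. Each cluster measured in two control periods and one FT period of its own | high 70s to about 98% | about 88–99% | 94% or more |
| C. Every cluster measured in every period | 88–98% | not tabulated | over 99% |

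Layouts A and C use c = 0.8 and (ρ, r) pairs (0.01, 0.5), (0.05, 0.5), (0.05, 0.7) and (0.10, 0.7), with 2, 4 and 7 steps. Layout B uses ρ 0.01–0.10, r 0.5–0.7 and c 0.8–1.0.

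At SD 19.4, the difference detectable with 80% power runs from about 3.5 points (layout C, 7 steps) to 13.0 points (layout A, 2 steps), against the 9.7 points implied by 0.5 SD.

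**The case against.** **The formula is not written out.** This stands: it is inferred from an exact match, and a paired test at 0.25 SD of the difference also gives 126. That alternative uses an effect the article does not state. Even if it were the true route, it would still contain no clustering or period term, so the conclusion does not depend on the choice.

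**A journal article may leave the ICC to the full protocol.** This is fair for an input that is merely unreported. Here the result is published too, and it equals the unadjusted value. An allowance for clustering or pairing would normally have moved N away from 126.

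**The comparison phrase is not wrong in itself.** This also stands. It can be read as end of control against end of intervention in the same people. With a staggered start, some later clusters may also still be in control when earlier ones finish. A reader might infer that no untreated comparison ever exists after the intervention. Section 2.1 does not support so absolute a statement.

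**The SD source does not affect N.** Correct if the effect is 0.5 SD, because the SD then cancels. The spinal cord injury source matters only when the effect is expressed in WHOQoL-Bref points.

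**Conclusion.** The stated 80% is not the power of this trial as designed and analysed. At 126 participants and 0.5 SD, plausible values run from about 53% to over 99%. The result depends on the ICC, within-person correlation, cluster autocorrelation, number of steps and measurement layout, none of which section 7.1 states. These ranges rest on assumed values and illustrate the spread; they do not bound the answer. They also rest on reading the stated 0.5 units as 0.5 SD.

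Two stronger readings are tempting. One is that the trial is underpowered, because the clustering-only figures all fall below 80%. Those figures ignore the own-control gain, and most of the stepped-wedge layouts examined exceed 80%. The other is that the own-control design makes 140 safely sufficient. The two-step own-period layouts can fall below 80%, so the article does not support that either. The defect is a mismatch between design and power calculation; the arithmetic itself reproduces.

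**What to change.** - Recompute power for the mixed model that will be fitted. State the number of clusters and steps, the group sizes at the two sites, the period effects and the primary contrast. Show results over a range of ICC, cluster autocorrelation and within-person correlation.
- Report the power and the detectable WHOQoL-Bref difference at 126 completers, and restate the figure for the planned sample. Do not say in advance that the sample is or is not adequate.
- Replace the 0.5 units wording with 0.5 SD (9.7 points at SD 19.4) if that was meant.
- Justify the spinal cord injury SD for adults with mental illness, or replace it if a suitable WHOQoL-Bref SD is available. The Introduction mentions quality-of-life results from the provider's earlier programs but gives no SD and names no instrument, so availability would have to be checked.

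The cost is a few hours of calculation and one rewritten paragraph. Whether recruitment needs to change can be judged only from the recomputed figure.

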### 1.2. Hypotheses

It is hypothesised that, compared to control data (initial 10-week assessment period for all participants), over the course of the FT intervention participants will show improvements in QoL, and psychosocial, psychological, and physical wellbeing.

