## 2. Methods

### 2.1. Design

This study will be a multi-site longitudinal stepped-wedge cluster randomised trial [49]. Each participant will complete an initial 10-week control period (with pre and post assessments) followed by the intervention in a group (cluster), thereby ‘acting as their own control’ [49]. Participants will be allocated to clusters in the order they enrol in the study, and commencement of each cluster will occur in random order [49]; randomisation will be conducted by author [name] using an online random permutation generator suggested by Suresh [50]. Randomisation information will be provided in writing to Link Workers at each site who will then liaise with the intervention clinician (author [name]) to commence clusters in the assigned order. Sites will complete the intervention sequentially.

Assessment timepoints include pre- and post-control period (assessments 1 and 2), pre- and post-intervention (assessments 3 and 4), and 5-weeks post intervention (assessment 5). Additional timepoints include pre (assessments A1–A10) and post (assessments B1–B10) all FT sessions. A flow diagram of study phases and assessment timepoints can be seen in Figure 1, below.

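### Section 7.1 sizes the trial for a two-group comparison that its control-then-intervention design and planned mixed model do not make

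*Protocol article*

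**What the plan says.** Four places in the protocol article bear on which comparison decides the trial.

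- **1.2 Hypotheses** expects that, "compared to control data (initial 10-week assessment period for all participants), over the course of the FT intervention participants will show improvements".
- **2.1 Design**: "Each participant will complete an initial 10-week control period (with pre and post assessments) followed by the intervention in a group (cluster"). Assessments 1 and 2 bracket the control period, 3 and 4 bracket FT, and 5 is the follow-up. Clusters start in random order.
- **7.1 Sample Size Estimation**: "Calculations indicate a sample of 126 participants is required", in order to "detect a minimum effect of 0.5 units (SD = 19.4"), the difference being one "between control and intervention conditions post-intervention". Alpha is 0.05 and power 0.8. Whether the test is one- or two-sided is not stated, and no within-person correlation or intracluster correlation (ICC) is given.
- **Analysis** names a linear mixed model following a published stepped-wedge method, chosen because it handles clustering and repeated measures.

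**The concern.** A sample size is meaningful only for the comparison it was computed for. Section 7.1 describes a difference in level between two conditions after the intervention, which is how one would describe a parallel-group trial. In this trial each participant supplies both control and FT data, in that order, and the analysis is a repeated-measures model. The variance of the FT effect then depends on the within-person correlation, the cluster ICC and the adjustment for time. None of these enters 7.1.

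The hypothesis adds a second ambiguity. With a before and an after assessment in each period, its natural reading is (assessment 4 minus 3) against (assessment 2 minus 1). That is a different quantity from end of FT against end of control, with a different variance and different sensitivity to what usual care does during the first 10 weeks. At stake is whether the 80% power refers to the result that will be reported, and whether readers will know in advance which contrast supports the hypothesis. The trial is unblinded (9.1), which is a further reason to settle this beforehand.

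**Working it through.** **Inputs.** From 7.1: effect 0.5 units, SD 19.4, alpha 0.05, power 0.80, N = 126. Assumed, because the article does not give them: a two-sided test, equal variances at all assessments, and a common within-person correlation rho between 0.3 and 0.9. Clustering and period effects are ignored throughout.

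**1. Reproducing 126.** For two independent groups, n per group = 2 × (1.960 + 0.842)² × (SD/effect)².

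| Reading | Total N |
|---|---|
| 0.5 units, SD 19.4, two independent groups, two-sided | 2 × 23,633 = 47,266 |
| Same, one-sided | 37,230 |
| 0.5 units, paired, SD of difference 19.4 | 11,817 |
| 0.5 SD (9.7 units), two independent groups, two-sided | 2 × 63 = **126** |
| 0.5 SD, two independent groups, one-sided | 100 |
| 0.5 SD of the difference, paired | 32 |

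Only the fourth row matches: 2 × 7.849 / 0.25 = 62.8, rounded up to 63 per group. A paired effect of 0.25 SD of the difference would also give 126 (7.849 / 0.0625 = 125.6), but 0.25 appears nowhere in the article. The number therefore points to a parallel-group calculation at 0.5 SD, with the effect mislabelled as 0.5 units.

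**2. Variance of the two within-person contrasts.**

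- End of FT against end of control (assessment 4 − 2): 2 × SD² × (1 − rho).
- Change against change, (4 − 3) − (2 − 1): 4 × SD² × (1 − rho).

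The ratio is 2 at any rho. The N needed for 80% power at 9.7 units, and the power with 126, are:

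| rho | N, 4 − 2 | N, change v change | Power with 126, 4 − 2 | Power with 126, change v change |
|---|---|---|---|---|
| 0.3 | 44 | 88 | 99.7% | 91.8% |
| 0.5 | 32 | 63 | >99.9% | 97.8% |
| 0.7 | 19 | 38 | >99.9% | 99.9% |
| 0.9 | 7 | 13 | >99.9% | >99.9% |

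No row returns the 126 participants at 80% power that 7.1 states.

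**3. Sign (illustration only; the article gives no trajectory).** Take means of 50, 56, 56 and 59 at assessments 1 to 4. Then 4 − 2 = +3, while (59 − 56) − (56 − 50) = −3. More generally, suppose FT has no effect:

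- Usual care gains 0.3 SD in the first 10 weeks and then plateaus: 4 − 2 gives 0.00, change against change gives −0.30 SD.
- Usual care gains 0.3 SD in each 10 weeks: 4 − 2 gives +0.30 SD, change against change gives 0.00.

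Each contrast is right under one pattern and biased under the other.

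**The case against.** The best defence is that the article does name one analysis framework, the stepped-wedge mixed model, and nowhere plans a change-score test. On that view 1.2 is a one-sentence hypothesis rather than a definition of the treatment effect, the post-intervention wording in 7.1 is loose shorthand for end of FT against end of control, and the exact model contrast can wait for an analysis plan. Much of this stands. Section 1.2 never uses the word change, so change against change is an inferred reading, and no direct contradiction between 1.2 and 7.1 is established.

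Three stronger conclusions are tempting and are not supported:

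- *That nobody is in control once participants are post-intervention.* This is true only on each participant's own timeline. Clusters start at staggered times, so one cluster can be finished while another is still in control, and a stepped-wedge model can use that comparison.
- *That the contrasts will give opposite answers.* The reversal above depends on invented means.
- *That the trial is underpowered.* At the 0.5 SD that reproduces 126, both within-person contrasts have ample power before clustering. Low power appears only if a smaller effect is assumed, and the article states none.

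The defence does not rescue 7.1. The shorthand reading fails on the number itself: at 0.5 SD, end of FT against end of control needs 44 participants or fewer for rho of 0.3 or more, not 126. The sample size is stated in this article, so its basis is not a detail left to another document.

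**Conclusion.** The point holds as a mismatch between the sample-size basis and the trial's design and analysis. The stated 126 and 80% power fit two independent groups of 63 at a standardised effect of 0.5. The trial instead passes everyone from control to FT and analyses repeated measures, so its actual power for the planned FT effect is unstated. It could be above or below 80%: pairing within persons raises it, while clustering and time adjustment lower it.

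The secondary ambiguity in 1.2 is real but rests on interpretation. If the hypothesis means change against change, that contrast carries twice the variance of end of FT against end of control (equal variances and correlations assumed) and can differ from it in sign when scores drift during control. The article does not say whether they will drift. The match to 126 also assumes a two-sided test and the normal approximation.

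**What to change.** Name one primary treatment contrast and use it in all three places: the FT effect (FT against control) from the planned linear mixed model, adjusted for time period and allowing for cluster and repeated measures.

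- **1.2**: word the hypothesis as a favourable FT effect in that model.
- **7.1**: replace the post-intervention wording with that contrast. Restate the power of the existing 126 completers and 140 recruits for it, giving the effect in explicit units (points or SD) and a range for within-person correlation and cluster ICC.
- **Analysis**: write out the model term that carries the FT effect and the time terms. Clients are recruited at intake, so say whether time since enrolment is addressed; calendar period alone does not remove that trend.
- **Sensitivity**: report change against change and end of FT against end of control as labelled sensitivity analyses that do not decide success, noting that each is biased under a different usual-care trajectory.

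The cost is wording in three paragraphs, one recalculation and the labelled sensitivity analyses. Recruitment and visits are unaffected. The downside is that the restated power may be less favourable than 80% once clustering and time effects are included, and that the choice of contrast is no longer open after the data are seen.
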